### Study of Secondary Variables

In addition, the study of secondary variables will allow us to compare our results with those of previous studies and provide additional knowledge in the specific population of healthy older adults with no fall history. As done in previous studies [35-37], some specific tests will be carried out before and after the intervention. First, in terms of functional capacities, we will evaluate mobility and balance capacities, which are linked to the risk of falls in older adults [57-59]. Second, in terms of psychological states, we will study motivation toward health-oriented physical activity [60], intrinsic motivation [61], and self-reported fear of falling [62,63], which may impact the risk of falls in older adults. The secondary variables will allow us to investigate the training program’s potential effects on some specific health components, given that interactions exist among gait behavior, functional capacities, and psychological states [64]. Recently, Dermody et al [43] reviewed the high potential of VR-HMD to improve both functional and psychological outcomes in older adults. Finally, in addition to the study of gait adaptability behavior and the acceptance of the XR device, the study of secondary variables will allow us to demonstrate potential general health changes after the gait training program.

## Methods

### Participant Recruitment

The initial recruitment will be carried out from an existing cohort of healthy older adults recruited by the Active Aging Chair.

### Inclusion Criteria and Informed Consent

Participants are independent-living community dwellers aged between 65 and 80 years. They are active older adults with weekly moderate to vigorous physical activity. This study is a part of a broader research program aimed at determining the extent to which new technologies (eg, exergames and XR) can be used to promote healthy aging among active older adults [23,24,65]. Of course, populations of more fragile older adults (eg, older adults who fall) could benefit from an appropriate intervention approach; however, our objective in this study consists, rather, within the framework of a preventive approach of creating the conditions allowing the delay or even avoidance of the occurrence of a first fall.

The exclusion criteria are inability to practice activity at a moderate or vigorous intensity (checked by medical examination supervised by cardiologists), moderate or severe cognitive impairments (ie, a Mini-Mental State Examination score <26 [66]), severe noncorrected visual impairments, and uncontrolled psychiatric disorders.

Every 5 minutes of VR use, the Fast Motion Sickness scale [67], designed to measure cybersickness, will be completed orally by the participant. According to the protocol set up by Keshavarz and Hecht [67], if a participant reaches a score of 15 or more, they will immediately be asked if they wish to stop participating and be told that this will have no harmful consequences for them.

Information about the organization of the gait training programs will be presented to the eligible participants by the principal investigator. Those who are willing to participate will be asked to give informed consent.

### Ethical Considerations

Importantly, this protocol will be submitted during April 2025 to a national ethics committee (ethics committee for research in science and technology of physical and sporting activities) for approval. The approved protocol will be implemented from September 2025 in accordance with the Helsinki Convention. Before the study, participants will give their written informed consent to participate for free in the experiment. For their part, the researchers who carry out the experiment undertake to respect the rules of data confidentiality and the privacy of the participants.

### Study Design

This study is based on a comparison of a gait training program in VR (ie, the VR group) with sessions of NW (ie, the NW group). Participants who meet the inclusion criteria will be randomly allocated to the gait training program (in the VR or NW group) using a computer-generated block randomization with a block size of 30 participants (1:1 rate). The data for participants in both groups will be obtained at 3 different times: 1 week before the beginning of the training program (T0), 1 week after completion of the training program (T1), and 1 month after completion of the training program (retention assessments; T2). Moreover, a follow-up (T3) with the incidence of trips and falls will be done during the 12 months after completion of the gait training program. Participants’ flow is presented in Figure 1.

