**Methods:**

We will be conducting a randomized controlled trial with pretests, posttests, retention tests, and follow-up. In total, 40 healthy independent-living community dwellers (aged between 65 and 80 years) will be allocated, after a general medical examination, to the VR or the NW group for a training program of 6 weeks. Primary outcomes related to gait adaptability capacities (ie, analysis of adjustments made in different locomotor tasks) and acceptance of the VR device (ie, analysis of acceptance) will be assessed before and after the intervention and 1 month after the completion of the training program (retention). A follow-up will be done during the 12 months after the completion of the gait training program.

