In summary, our software will allow us to implement the main principles of Hendry et al [45] presented in the introduction. The VR training program was designed in particular to optimize the variability of the practice conditions and to allow the learner to have qualitative feedback on the success of the task. The variability of the practice conditions was obtained essentially by manipulating the location of the obstacles, their dimensions, and the nature of the task. The speed of locomotion was not manipulated as such, given that participants were asked for each trial to complete the route as quickly as possible while giving priority to precision. Concerning feedback, at the end of each trial, the participant will have the possibility of requesting feedback related to the knowledge of result (self-controlled feedback). It has been shown that this type of feedback makes it possible to enhance learning by placing the participant at the heart of the learning experience and developing their autonomy [69-71]. One of the main advantages of the self-controlled feedback procedure is that it allows participants to use feedback to optimize control processes without inducing a dependency effect. Indeed, the literature indicates that participants spontaneously implement a fading procedure [71] by requesting feedback massively at the start of the training period and then less often, which protects them from any dependence on feedback [50].

A stratified randomization (with the sex factor) will be conducted, using a computer software program to generate a random sequence. Two strata (male and female) will be identified, and randomization will be applied to each stratum. For instance, when a male older adult participates in the study, he will be the first to be allocated to the male strata, and the group (VR group and NW group) will be determined through randomization applied to the male stratum.

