#### Sample Size

The sample size calculation was performed using G*Power (version 3.1.9.7). To detect relevant within-between-group differences, we calculated a sample size sufficient to detect small effect sizes. On the basis of values generally observed in studies conducted in the field of acceptability and acceptance of technologies in general (because no study similar to ours has yet been conducted), f=0.2, α=.05, and *P*=.80 were chosen to favor clinically significant effect sizes [79]. To test the main hypotheses of this study, 50 participants are required. To compensate for possible dropouts, 5 more participants will be included in each group. The 2 groups will be composed of 30 participants each.

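### Two descriptions of the randomisation are not reconciled, and a block of 30 is too large to protect the sex stratification in a trial of 40 to 60 people

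*Protocol article*

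**What the plan says.** Study Design in the protocol article allocates eligible participants "using a computer-generated block randomization with a block size of 30 participants (1:1 rate". It mentions no stratification factor.

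The last paragraph of the VR Group section, after the description of the training software, returns to allocation: "A stratified randomization (with the sex factor) will be conducted, using a computer software program to generate a random sequence". It continues: "Two strata (male and female) will be identified, and randomization will be applied to each stratum". It gives no block size and does not refer back to Study Design.

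The number to be randomised also differs. The abstract says "In total, 40 healthy independent-living community dwellers (aged between 65 and 80 years) will be allocated". Sample Size says "To test the main hypotheses of this study, 50 participants are required", adds 5 per group for dropout, and concludes: "The 2 groups will be composed of 30 participants each".

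**The concern.** Whoever builds the allocation list has to know the strata and the block size within each stratum. The article gives the two parts in separate places and does not say whether they belong together. Put together, they give blocks of 30 inside two strata of a trial with 60 people at most. A stratum that stops partway through such a block is only loosely balanced.

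The sponsor chose sex as the factor to balance, so the first thing at stake is whether the list delivers that. Second is whether the arms reach the planned 30 each. Third is whether the procedure could be reproduced from the text. The block size equals the planned size of one group, so it may be the group size reported by mistake as a block size. That is an inference; the article does not say so.

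**Working it through.** **Inputs.** Block size 30 and ratio 1:1 (Study Design). Two strata, male and female (VR Group, last paragraph). Totals of 60 (Sample Size) and 40 (Abstract). The number of men is not given; 15 to 30 is assumed for a total of 60 and 12 to 20 for a total of 40.

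**The plan's own figure.** 50 + 2 × 5 = 60 = 2 × 30, as stated. A block of 30 goes into 60 exactly twice.

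**Formulas.** Let D be the number in the VR arm minus the number in the NW arm. If a list stops after k places of a block of 30, the VR count is hypergeometric and var(D) = k(30 − k)/29. Without blocks, var(D) = n. The variances of the two sex strata add. Probabilities come from the exact distributions.

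**1. Blocks of 30, no strata.**
- 60 randomised: k = 0, so D = 0 and the arms are 30:30 with certainty.
- 40 randomised: k = 10, var(D) = 10 × 20/29 = 6.90, SD 2.6. The largest difference is 10 (25:15); P(|D| ≥ 4) = 0.25 and P(|D| ≥ 6) = 0.05.
- Sex, 60 randomised, m men arriving in random order: the variance of the difference in men between arms is m(60 − m)/59. For m = 20 it is 800/59 = 13.56, SD 3.7; for m = 30 it is 900/59 = 15.25, SD 3.9. The probability that the arms differ by 6 or more men is 0.17 for m = 20, 0.12 for m = 25 and 0.20 for m = 30.

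**2. Blocks of 30 within each sex, 60 randomised.**

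| Men/women (assumed) | var(D) | SD | Largest difference | P(difference ≥ 6) |
|---|---|---|---|---|
| 30/30 | 0 | 0 | 0 | 0 |
| 25/35 | 125/29 + 125/29 = 8.62 | 2.9 | 10 | 0.08 |
| 20/40 | 200/29 + 200/29 = 13.79 | 3.7 | 20 | 0.17 |
| 15/45 | 225/29 + 225/29 = 15.52 | 3.9 | 30 | 0.20 |

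At a total of 40 the probability is 0.17 for 20/20, 0.15 for 15/25 and 0.10 for 12/28. Within one stratum of 15, the chance of a 9:6 or worse split is 1 − 2 × 6435²/155,117,520 = 0.47.

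**3. No blocks within sex.** At 60, SD = √60 = 7.7, P(difference ≥ 6) = 0.52 and P(difference ≥ 10) = 0.25, whatever the sex mix.

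**4. How well sex itself is balanced, 20 men among 60.** The chance that the arms differ by 6 or more men (13:7 or worse) is 0.17 with unstratified blocks of 30, 0.05 with blocks of 30 within sex, and 0.26 with no blocks within sex.

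**5. Efficiency.** Relative efficiency of unequal arms is 4·n₁·n₂/N². For 33:27 it is 3564/3600 = 0.990; for 35:25 it is 3500/3600 = 0.972. The loss is 1% to 3%.

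**6. Small blocks within sex.** Blocks of 4 limit the difference to 2 per stratum and 4 overall, for any sex mix. With blocks of 4 and 6 mixed, the limit is 3 per stratum and 6 overall. A difference of 6 needs both strata to stop at the third place of a block of 6 with all three in the same arm; given such stops, the probability is 2 × (1/20)² = 0.005.

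**The case against.** The two passages can be read together. Study Design does not mention strata and the VR Group section does not mention blocks, but neither excludes the other, and stratified block randomisation is a familiar combination. A reader might infer that the schemes are incompatible, or that the second means simple randomisation within sex. The text supports neither; it is silent. The unblocked figures (SD 7.7) apply only if that silence meant no restriction.

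A reader might also infer that neither description yields balanced groups, or that stratification achieves nothing without small blocks. Both are too strong. Study Design alone gives exactly 30:30 at the planned 60. At a 20/40 split, blocks of 30 within sex roughly halve the SD of the arm-size difference, from 7.7 to 3.7. Unequal arms of the likely size cost almost no power. Large blocks are also harder to predict, which has some value where participants and trainers necessarily know the arm.

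All of this stands, and it reduces the weight of the point. It does not supply the missing link between the two passages. Nor does it make 30 a suitable block size inside strata that are unlikely to fill a block. The block size is a rule the article states, not a detail left to a fuller document.

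**Conclusion.** The concern holds in limited form: the descriptions are unreconciled, and no reading of them reliably secures both arm size and sex. Unstratified blocks of 30 secure arm size only if the total is a multiple of 30, and leave sex uncontrolled. Blocks of 30 within sex secure both only if each sex numbers a multiple of 30. Otherwise, for 60 people, the chance of an arm-size difference of 6 or more is about 0.08 to 0.20 over the splits examined. Allocation without restriction within sex, if that was meant, would balance neither.

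The size of the problem depends on the sex mix, which is assumed, and on whether 40 or 60 are randomised, which the article leaves open. The cost in power is small. What is lost is protection of the stratification factor and a procedure that can be reproduced.

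A reader might go further and conclude that allocation precedes the baseline tests, because acceptance is asked of the VR group only and is scheduled at T0. The article does not establish this: gait testing, then allocation, then the questionnaire would also fit.

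**What to change.** State one scheme in one place: 1:1 allocation, stratified by sex, with small permuted blocks of varying size (for example 4 and 6) within each stratum, from a computer-generated list concealed from those who enrol and train participants. Delete the block of 30. Include sex in the analysis model, since it is a stratification factor. Reconcile the abstract's 40 with the 60 in Sample Size.

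The cost is one regenerated list, a few lines of text and one extra model term. Small blocks are slightly more predictable where the arm is known to participants and trainers; varying sizes and concealment limit this. If enrolment has begun, report the scheme actually used instead.

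Optional: if allocation does precede the T0 gait tests, do the gait and functional tests before the arm is revealed and give the VR-only acceptance questionnaire afterwards.

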**Figure 1 figure1:**
[figure not shown]
Flowchart of the study design. MMSE: mini-mental state examination; NW: Nordic walking; VR: virtual reality.

### Gait Training Programs: NW Versus VR

#### Overview

The 2 gait training programs will be dose-matched in terms of duration (ie, 45 min per session) and frequency (ie, 3 sessions per week) of training over a 6-week program (ie, 18 training sessions) following the methodology used in previous gait training studies [35-37]. Previous studies have shown that extensive practice is important for the consolidation and retention of motor memory [68]. Therefore, in line with our ambition to develop long-term improvements in gait adaptability behavior, a large amount of practice in our gait training programs is necessary.

#### NW Group

In the NW group, participants will practice the training sessions in a nature park. They will be instructed to walk with poles continuously around the park. Each training session will consist of a warm-up period (10 min), main exercise (45 min), and cool-down period (5 min). Participants will adapt their locomotion to uneven terrain. They will negotiate natural obstacles such as avoiding a rock or crossing over a tree root, thus improving their gait adaptability capacities. Sessions will be provided by a coach from a multisport club proposing programs of physical activity adapted to older adults. Participants will follow the coach, who will progressively increase the level of difficulty over the 6 weeks, show the way, and adapt to the gait speed.

#### VR Group

In the VR group, participants will practice the training sessions in an experimental room. In 1 training session, participants will negotiate 60 trials. Sessions will be provided by the principal investigator. Participants will practice gait training sessions in a fully immersive VR. A wireless HTC Vive Pro VR-HMD will be used to display VE (Figure 2A). Participants will wear HTC Vive Pro foot trackers on their feet, which will record their feet positions (in relation to obstacles) and display 2 virtual foot avatars in the VE. A security system consisting of a safety harness (Figure 2C) connected to an in-ceiling rail by a lanyard (Figure 2B) will provide training sessions in a safe context. This setup has been validated in a previous study [44] in which gait adaptability behavior was similar in the real world and in VR.

**Figure 2 figure2:**
[figure not shown]
Test equipment. (A) A wireless HTC Vive Pro will be used to display the virtual environment. Two HTC Vive Pro 2.0 trackers will be used to record the positions of the feet and display virtual 3D shoes in the virtual environment; (B) in-ceiling rail; (C) safety harness.

VR training sessions were created with homemade software developed with Unreal Engine (version 5.1; Epic Games) and OpenXR (Khronos Group). It will be used with a wide panel of AR and VR technologies (Oculus, HTC Vive, HP, etc). The software contains 2 operation modes: design and simulation.

The design mode is used to create the content of the different training sessions (ie, 60 trials in different configurations per training session) with a user interface. Each kind of task can be modulated *ad infinitum* by changing the position, number, and size of the obstacles. Moreover, configurations will be modulated by the number of different tasks displayed: participants can negotiate one or several kinds of tasks in 1 trial. The 3 tasks mainly used in the training protocols are illustrated in Figure 3. The pointing task consists of positioning the foot as close as possible to the line without exceeding it. The crossing-over task consists of crossing over a horizontal obstacle without meeting it. The stepping-over task consists of stepping over a vertical obstacle without touching it. The technology used (tracker positioned on the feet) makes it possible to locate the feet at any time with reference to virtual obstacles and to determine the performance produced depending on whether the task is carried out in accordance with the success criteria or, conversely, if collisions with obstacles occurred. This method is based on the exclusive use of virtual obstacles. Examples of different trial configurations are provided in Figure 3. In this mode, different criteria of success will be determined at different scales (ie, obstacle, trial, and training session). The criterion of success for each obstacle negotiation is fixed according to the kind of task: pointing accuracy (in cm) for simple locomotor pointing; recovery (in cm) for successive locomotor pointing; and clearance (in cm) for stepping-over, crossing-over, and obstacle avoidance. The criterion of success for each obstacle is set as a certain percentage of successful obstacle negotiation. Finally, the criterion of success for each training session is set as a certain percentage of successful tasks.

The simulation mode is used to display the training sessions created in the design mode and to record participants’ foot positions in relation to obstacles. In this mode, the participant’s anthropometric data are considered to propose individualized session content based on a certain percentage of each participant’s leg length. In real time, the participants’ performance is calculated in terms of obstacle negotiation and completion time. On the basis of these real-time data, the success or failure of the obstacle negotiation will be measured depending on the determined criterion of success. Different types of feedback can be provided to inform the participant about their obstacle negotiation performance. Moreover, at the end of the trial and the training session, additional feedback can be given to inform the participant about their trial and session success, respectively. This feedback can be provided on the screen as text (“success” or “fail”) or coloration of the virtual scene (in green for success or in red for fail).

Given that the software allows the modulation of the content of the training sessions by setting specific criteria, several goal-directed tasks in various VEs will be provided to propose relevant gait adaptability exercises. Six different VEs have been created (Figure 4): subway, shopping center, forest, beach, office, and street.

**Figure 3 figure3:**
[figure not shown]
Schematic of the 4 different goal-directed tasks performed on the walkway GaitRite (in gray). (A) simple locomotor pointing task; (B) crossing-over task; (C) stepping-over task; and (D) “mixed condition” with 2 locomotor pointing (in purple), 1 crossing-over (in green), and 1 stepping-over (in orange) tasks.

**Figure 4 figure4:**
[figure not shown]
Examples of first-person views of locomotor goal-directed tasks in the different virtual environments (A) cross over road tar in a street, (B) step over a pipe and stepping on successive flyers in a subway, (C) avoid cardboard boxes in a shopping center, (D) step over successive seashells on the beach, and (E) step over successive leaves in a forest, (F) avoid chairs in an office. Green areas represent the start and the finish lines.

Our gait training sessions will be developed with an increasing level of difficulty over the 6 weeks. In terms of progress, 18 levels of difficulty have been created (to be able to provide a new level per new training session). In the first training sessions, only one kind of task will be displayed in a single trial in the presence of a limited number of mainly small obstacles. Progressively, the number and size of the obstacles will increase. Afterward, 2 kinds of tasks will be displayed in a trial. In the last training sessions, participants will negotiate various obstacles with 2 kinds of tasks in a trial. On the basis of the criteria of success previously presented, when a participant succeeds in the training session, they advance to the next level of difficulty for the next training session. Conversely, if they fail, they remain at the same level for the next training session. In addition, the session content has been created with a high level of individualization. As presented earlier, the participant’s anthropometric data will be considered to propose training according to individual capabilities. The obstacle sizes will be proportional to each participant’s leg length. The surface area, the height, and the depth of the obstacle will be modulated, respectively, for the successive locomotor pointing, stepping-over, and crossing-over tasks. Obstacle modulation will lead to equivalent levels of difficulty for all the participants over the training program.

In summary, our software will allow us to implement the main principles of Hendry et al [45] presented in the introduction. The VR training program was designed in particular to optimize the variability of the practice conditions and to allow the learner to have qualitative feedback on the success of the task. The variability of the practice conditions was obtained essentially by manipulating the location of the obstacles, their dimensions, and the nature of the task. The speed of locomotion was not manipulated as such, given that participants were asked for each trial to complete the route as quickly as possible while giving priority to precision. Concerning feedback, at the end of each trial, the participant will have the possibility of requesting feedback related to the knowledge of result (self-controlled feedback). It has been shown that this type of feedback makes it possible to enhance learning by placing the participant at the heart of the learning experience and developing their autonomy [69-71]. One of the main advantages of the self-controlled feedback procedure is that it allows participants to use feedback to optimize control processes without inducing a dependency effect. Indeed, the literature indicates that participants spontaneously implement a fading procedure [71] by requesting feedback massively at the start of the training period and then less often, which protects them from any dependence on feedback [50].

A stratified randomization (with the sex factor) will be conducted, using a computer software program to generate a random sequence. Two strata (male and female) will be identified, and randomization will be applied to each stratum. For instance, when a male older adult participates in the study, he will be the first to be allocated to the male strata, and the group (VR group and NW group) will be determined through randomization applied to the male stratum.

